### Strategies to improve adherence to interventions

The use of non-steroidal anti-inflammatory drugs (NSAIDs) or tramadol as rescue medication is permitted during the study period. Allowed medications are limited to ibuprofen (maximum 1,200 mg/day) or naproxen (maximum 1,000 mg/day) or tramadol at a maximum 400 mg/day administered orally in divided doses as needed for pain control. Patients are instructed to use rescue medication at the lowest effective dose and to maintain consistent usage patterns, when possible, throughout the follow-up period.

The type, dose, and frequency of NSAID use will be recorded at each follow-up visit and included in the statistical analysis to assess potential confounding effects.

Additional invasive interventions targeting lumbar disc herniation, such as nerve blocks or spinal cord stimulation, are not permitted during the study period, as they may directly influence pain and functional outcomes.

All clinical staff involved in administering the intervention will receive comprehensive training on the protocol. Each center is also provided with easy access to detailed protocol documentation, including visual aids and quick-reference guides that summarize key points of the protocol. Periodic audits will be conducted at each center to review adherence to the protocol.

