### Measurement of clinical outcomes

Baseline demographic characteristics, including gender, age, education level, occupation, smoking history, allergy history, family medical history, history of diabetes, and current use of analgesics, will be assessed, in addition to patient measurements such as height, weight, the level of lumbar disc herniation, and the severity of nerve compression measured by Pfirmann grading system base on lumbar MRI (Grade I: Herniated disc in contact with the nerve root without displacement; Grade II: Herniated disc in contact with the nerve root, no nerve root displacement; Grade III: Herniated disc in contact with the nerve root, causing posterior displacement of the nerve root; Grade IV: Herniated disc in contact with the nerve root, compressing it against the posterior wall of the spinal canal) (Majeed et al., 2016). Laboratory parameters, including fasting blood glucose and morning serum cortisol levels will also be measured. Pain intensity will be evaluated using the NRS for both low back pain and leg pain. The Oswestry Disability Index (ODI) and Roland-Morris Disability Questionnaire (RMDQ) will be used to assess functional disability. Generalized Anxiety Disorder 7 (GAD-7) and Patient Health Questionnaire 9 (PHQ-9) were used to assess anxiety and depression.

Follow-up assessments will be conducted at post-injection day 1, week 1, week 2, week 4, week 8, and week 12 (Table 1).

**TABLE 1 T1:** Schedule of enrolment, interventions, and assessments.

Timepoint	Enrolment	Baseline	Allocation	Follow up					
	​	​	0	*Day1*	*Week* *1*	*Week* *2*	*Week* *4*	*Week* *8*	*Week* *12*
Enrolment									
Eligibility screen	X	​	​	​	​	​	​	​	​
Informed consent	X	​	​	​	​	​	​	​	​
Allocation	​	​	X	​	​	​	​	​	​
Interventions									
Dexamethasoe palmitate	​	​	X	​	​	​	​	​	​
Combined betamethasone	​	​	X	​	​	​	​	​	​
Assessmens									
*Pain intensity (NRS score)*	​	X	​	X	X	X	X	X	X
*ODI score*	​	X	​	​	​	​	X	X	X
*RMDQ score*	​	X	​	​	​	​	X	X	X
*PHQ-9*	​	X	​	​	​	​	X	X	X
*GAD-7*	​	X	​	​	​	​	X	X	X
*Serum cortisol* *Levels blood glucose*	​	X	​	​	​	​	X	​	​
*Satisfaction*	​	​	​	​	​	​	X	​	​
*Adverse event*	​	​	​	X	X	X	X	X	X

The primary outcome of this study is leg pain measured by NRS score which is measured on a scale of 0–10, with 0 indicating “no pain” and 10 indicating “the worst pain imaginable” at 4 weeks after procedure.

The secondary outcomes are:

Pain: NRS scores at 1 week, 2 weeks, 8 weeks, and 12 weeks post-injection.

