Functional disability: ODI and RMDQ at 4 weeks, 8 weeks, and 12 weeks post-injection.

Mental health assessment: GAD-7 and PHQ-9 at 4 weeks, 8 weeks, and 12 weeks post-injection.

Biochemical markers: Morning serum cortisol levels at 4 weeks post-injection. For participants with a pre-existing diagnosis of diabetes, fasting blood glucose will be monitored daily for seven consecutive days post-injection.

Patient satisfaction: Patient satisfaction will be evaluated at 4 weeks post-injection using a structured questionnaire. Satisfaction will be rated on a five-point Likert scale: very dissatisfied, dissatisfied, neutral, satisfied, and very satisfied. In addition, patients will provide a global impression of treatment effect, categorized as: marked improvement, moderate improvement, slight improvement, no change, mild deterioration, moderate deterioration, or severe deterioration.

Throughout the follow-up period, patients will be allowed to continue their pre-existing medication regimens. Concomitant medication use, including nonsteroidal anti-inflammatory drugs (NSAIDs), tricyclic antidepressants (TCAs), and gabapentinoids, will be recorded in detail at each visit, including type, dose, frequency, and duration.

Incidence of adverse events defined as any unintended and harmful outcome that occurs during or after the procedure, which may be directly or indirectly associated with the intervention.

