### Primary outcome analysis

The primary outcome (NRS score at 4 weeks) will be analyzed using a linear mixed-effects model, including treatment group, time, and their interaction as fixed effects, with study center as a random effect, baseline NRS score will be adjusted as a covariate.

Non-inferiority will be assessed based on the between-group difference in mean NRS score at 4 weeks post-treatment, with a pre-specified non-inferiority margin of one point. Non-inferiority will be concluded if the upper bound of the two-sided 95% confidence interval for the between-group difference does not exceed the non-inferiority margin. Both intention-to-treat (ITT) and per-protocol (PP) analyses will be performed to ensure robustness of the results.

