### Secondary outcome analysis

The secondary outcomes of this study are leg pain scores at multiple follow-up time points, functional disability (ODI and RMDQ), mental health assessment (GAD-7 and PHQ-9), and biochemical markers. For leg pain, the NRS scores for leg pain will be analyzed at each follow-up time point using Mixed-Effects Linear Models to account for repeated measurements and intra-patient correlation. This model includes fixed effects for treatment, time, and the interaction between treatment and time. Random intercepts are used to model individual variability over time. Functional disability scores are assessed via changes in ODI and RMDQ measured at 4, 8, and 12 weeks using Mixed-Effects Linear Models. Both measures are treated as continuous variables, and the analysis accounted for repeated measurements within patients. Mental health assessments will be completed using GAD-7 and PHQ-9 anxiety and depression scores, respectively, using Mixed-Effects Linear Models at 4, 8, and 12 weeks. Serum cortisol levels at 4 weeks will be compared between treatment groups using Student’s t-test for normally distributed data, and the Mann–Whitney U test for non-normally distributed data after assessment of normality.

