### Subgroup analysis

Prespecified subgroup analyses will be conducted to explore potential effect modifiers, including injection approach (interlaminar vs. transforaminal), herniation severity (Pfirmann grading system based on lumbar MRI), and patient characteristics such as age, sex, and presence of diabetes. Continuous outcomes (NRS, ODI, RMDQ, GAD-7, PHQ-9) will be analyzed using Mixed-Effects Linear Models with fixed effects for treatment, time, subgroup factor, treatment-by-time, and treatment-by-subgroup interactions, and random intercepts for patients to account for repeated measurements.

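### As-needed NSAID use after injection is to be analysed as a potential confounder, with tramadol left out; the primary non-inferiority test is not affected

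*Protocol article*

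**What the plan says.** In the protocol article, the section *Strategies to improve adherence to interventions* permits ibuprofen, naproxen or tramadol as rescue throughout the study, including "tramadol at a maximum 400 mg/day administered orally in divided doses as needed for pain control". The same section then states the analytic role of these data: "NSAID use will be recorded at each follow-up visit and included in the statistical analysis to assess potential confounding effects". Tramadol is not in that sentence.

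The section *Measurement of clinical outcomes* lets patients continue their existing medication and adds: "Concomitant medication use, including nonsteroidal anti-inflammatory drugs (NSAIDs), tricyclic antidepressants (TCAs), and gabapentinoids, will be recorded in detail at each visit". It gives these records no role in the analysis. The baseline list in the same section covers "history of diabetes, and current use of analgesics, will be assessed".

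The primary model is described as "including treatment group, time, and their interaction as fixed effects, with study center as a random effect, baseline NRS score will be adjusted", and the decision rule is: "Non-inferiority will be concluded if the upper bound of the two-sided 95% confidence interval for the between-group difference does not exceed the non-inferiority margin".

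**The concern.** A confounder is a common cause of treatment and outcome. Randomisation assigns treatment independently of anything a patient does later, so medication taken on demand after the injection cannot confound the comparison. It can be a consequence of pain, and hence of the assigned steroid. Conditioning on it gives a treatment coefficient that answers another question.

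The risk is one of interpretation. A difference labelled as adjusted for confounding, printed beside the primary result, looks like the better estimate although it is not. In a non-inferiority trial it could make a real deficit of dexamethasone palmitate look smaller or larger than it is.

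The NSAID-only scope adds a second problem. If one arm needs more rescue, readers need the total to interpret similar pain scores, and a look at NSAIDs alone would show only part of it.

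**Working it through.** **1. The plan's own figure.** From *Study sample size*: SD 2.2, margin 1, true difference 0, one-sided α 0.025, power 0.90.

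n per arm = 2 × (1.960 + 1.282)² × 2.2² / 1² = 2 × 10.51 × 4.84 = 101.7, so 102. With 10% loss: 102 / 0.90 = 113.3, so 114. Both figures reproduce, and this point disputes neither.

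**2. Where medication enters the stated models.**

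| Section | Stated terms | Medication term |
|---|---|---|
| Primary outcome analysis | "including treatment group, time, and their interaction as fixed effects, with study center as a random effect, baseline NRS score will be adjusted" | none |
| Secondary outcome analysis | "This model includes fixed effects for treatment, time, and the interaction between treatment and time" | none |
| Subgroup analysis | "fixed effects for treatment, time, subgroup factor, treatment-by-time, and treatment-by-subgroup interactions" | none |

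The promised confounder analysis therefore lies outside every model the article sets out.

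**3. Why conditioning changes the target.** Take a simple linear case. Rescue-free pain P differs by d between arms, with within-arm SD σ. Rescue is R = bP + noise of variance 1. Observed pain is Y = P − eR.

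- Unadjusted difference: d(1 − eb)
- Difference conditional on R: d / (1 + b²σ²)

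With σ = 2.2, b = 0.25, e = 0 and d = 1, the unadjusted difference is 1. The conditional one is 1 / (1 + 0.0625 × 4.84) = 1 / 1.3025 = 0.77, which agrees with simulation (0.77). If d = 0, both are 0.

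The opposite shift is also possible. If, within arm, the pain that prompts rescue is unrelated to week-4 pain, conditioning moves the estimate towards the rescue-free difference. In the scenarios of step 4 that is 1.06–1.27 when the observed difference is 1.0. The documents do not fix the direction.

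**4. Illustration of NSAID-only adjustment, as the sentence is worded.**

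- From the plan: 102 per arm, SD 2.2, margin 1, baseline NRS as covariate.
- Assumed: control mean 3.5; baseline to week-4 correlation 0.3; rescue probability logistic (slope 1, midpoint 4.5 or 6) in a pain score correlated 0 to 1.0 with week-4 pain; each rescue lowers NRS by 0.5, 1.0 or 1.5; tramadol and NSAIDs equally effective.
- Method: week-4 ANCOVA, 10,000 trials per scenario, observed difference set to 1.0, counting trials with the 95% upper limit below 1. Centre, repeated measures and continued pre-existing medication were not simulated.

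| Analysis | Mean difference | Non-inferiority declared |
|---|---|---|
| No medication term | 1.0 (set) | 2.2–2.8% |
| NSAID term, half of rescue is tramadol | 0.89–1.10 | 1–6% |
| NSAID term, a quarter of rescue is tramadol | 0.80–1.17 | 0.5–12% |

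At a true difference of 0, the plan's own assumption, all simulated means (6,000 trials) lie within 0.01 of 0.

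**5. What an NSAID-only comparison would show.** In the scenarios with more rescue, use is 36% in the control arm against 51–54%, a gap of 15–18 percentage points. If half of it is tramadol, NSAID use is 0.5 × 36 = 18% against 0.5 × 51 to 0.5 × 54, about 26–27%. The visible gap is 7.5–9 points, half the real one.

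**The case against.** The best defence is that the sentence names no covariate, model or adjusted estimate. A by-arm comparison of use would also satisfy it, and the detail may sit in an analysis plan that is not shown. This stands in part: the wording does not strictly commit to covariate adjustment. But the stated purpose is to assess confounding, and that rationale is wrong for as-needed use after injection, however the detail is filled in.

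Second, follow-up NSAID use is not all rescue. Patients may continue existing regimens and are asked to keep their use steady, so part of what is recorded is prognostic and not caused by treatment. This stands, and the illustration leaves it out. The legitimate way to use that part is through the baseline record.

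Third, NSAID may be shorthand in a condensed article, and the list of recorded concomitant drugs is open. A reader might infer that tramadol will go unrecorded; the documents do not support that. The gap is in the stated analysis only.

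Two stronger readings are also tempting:

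- *The non-inferiority test is biased.* It is not, as written: its model has no medication term and its rule is fixed on that model.
- *Adjustment would inflate false non-inferiority to 9–27% or more.* Such figures come from adjusting for all rescue, with rescue driven entirely by week-4 pain. The sentence promises neither. With weak correlation (0–0.2), the same all-rescue adjustment gives 0.1–3%.

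**Conclusion.** The point holds as a minor correction to one stated analysis. Post-injection as-needed NSAID use is wrongly cast as a potential confounder, and omitting tramadol would make any look at rescue use incomplete. The primary test, its decision rule and the sample size are untouched.

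That the rationale is wrong follows from the design and needs no assumed number. The size does need them: rescue rates, drug effect, the link between pain and use, and the tramadol share are all absent from the article. The simulated ranges straddle the nominal 2.5%, and neither a size nor a direction of bias can be claimed for this trial. They apply only if the medication term is fitted.

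**What to change.** Replace the sentence in *Strategies to improve adherence to interventions* with:

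*NSAID and tramadol use after injection (type, dose, frequency) will be recorded at each visit and compared between arms to help interpret non-inferiority. It will not be a covariate in the treatment-effect models. Any adjustment for analgesics will use baseline analgesic use only.*

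Baseline analgesic use is already collected, so no new measurement is needed for the last clause. The cost is one additional table by arm, with no extra patients or visits. The downside is that any arm difference in rescue use must be discussed alongside the primary result.

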### Statistical analyses

Descriptive statistics are used to summarize baseline characteristics (e.g., demographic information, clinical variables). Continuous variables are presented as mean with standard deviation or median with interquartile range, depending on the distribution of the data. Categorical variables are presented as frequencies and percentages. Statistical analysis is performed by investigators blinded from the allocation group, according to the per protocol and intention-to-treat principles.

### Primary outcome analysis

The primary outcome (NRS score at 4 weeks) will be analyzed using a linear mixed-effects model, including treatment group, time, and their interaction as fixed effects, with study center as a random effect, baseline NRS score will be adjusted as a covariate.

Non-inferiority will be assessed based on the between-group difference in mean NRS score at 4 weeks post-treatment, with a pre-specified non-inferiority margin of one point. Non-inferiority will be concluded if the upper bound of the two-sided 95% confidence interval for the between-group difference does not exceed the non-inferiority margin. Both intention-to-treat (ITT) and per-protocol (PP) analyses will be performed to ensure robustness of the results.

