## Methods and analysis

### Study design

This is a two-arm multi-center, non-inferiority, randomized double-blind controlled trial. Patients with clinically confirmed lumbar disk herniation and radicular pain will be randomly assigned to one of two treatment arms: image guided epidural injection of DEP or combined betamethasone through an interlaminar or transforaminal approach. Follow up will be conducted at 1 day, 1 week, 2 weeks, 4 weeks, 8 weeks, and 12 weeks post-treatment. Pain intensity will be evaluated at all follow up time points, functional outcomes and mental health will be evaluated at 4 weeks, 8 weeks, and 12 weeks follow-up time points. Safety outcomes, including side effects and adverse events will be assessed at 1 day and 4 weeks after treatment. For patients with a pre-existing diagnosis of diabetes, fasting blood glucose levels will be monitored daily for seven consecutive days postoperatively to evaluate the impact of steroids on glycemic control. A repeat injection will be administered based on the patient’s response at 4 weeks of follow-up.

Approval for this study was obtained from the Research Ethics Committee of all the center (approval reference number: 2024-457, 2025-251001, 2024K095, KY-2024-003-02, 2025-06, 2024-41, 2025-002). The trial was registered in the Chinese Clinical Trial Registry (Trial number: ChiCTR2400093970, https://www.chictr.org.cn, Chinese Clinical Trial Registry, 2024-12-15) and the trial protocol followed the ‘Standard Protocol Items: Recommendations (SPIRIT) guideline (Schulz et al., 2010). Patient consent was obtained after enrollment in accordance with the Declaration of Helsinki.

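### The primary leg-pain model is a repeated-measures model with no stated within-patient correlation and no stated coding of time, so the week-4 interval that decides non-inferiority is sound only under conditions the protocol does not fix.

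*Protocol article*

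**What the plan says.** The section Primary outcome analysis gives the confirmatory model as a linear mixed model "including treatment group, time, and their interaction as fixed effects, with study center as a random effect, baseline NRS score will be adjusted" for. No patient effect and no within-patient covariance is named, and the coding of time is not given. The same section ties the decision to this model: "Non-inferiority will be concluded if the upper bound of the two-sided 95% confidence interval for the between-group difference does not exceed" the margin of one point.

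Pain is measured repeatedly. Study design states: "Pain intensity will be evaluated at all follow up time points". Measurement of clinical outcomes lists six post-injection visits: "Follow-up assessments will be conducted at post-injection day 1, week 1, week 2, week 4, week 8, and week 12".

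The other leg-pain models are described differently. Secondary outcome analysis covers leg NRS "using Mixed-Effects Linear Models to account for repeated measurements and intra-patient correlation". It adds: "This model includes fixed effects for treatment, time, and the interaction between treatment and time", and "Random intercepts are used to model individual variability over time". Subgroup analysis specifies "random intercepts for patients to account for repeated measurements".

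**The concern.** Time and treatment-by-time terms have a purpose only if several visits per patient enter the fit. If study center is then the only random effect and the residual errors are independent, the model takes a patient's six scores as independent given center, treatment, time and baseline. Scores from one patient will not be.

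The article describes the correlation structure for the secondary and subgroup leg-pain models and leaves it out only for the model that carries the non-inferiority decision. An analysis plan that follows the primary section literally would inherit the gap.

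At stake is the standard error of the week-4 difference. If it is too small, the upper limit falls below the margin too often when the new drug really is one point worse. If it is too large, power is lost.

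**Working it through.** **Inputs from the protocol (Study sample size).** Margin 1, SD 2.2, true difference 0, one-sided alpha 0.025, power 0.90, 1:1 allocation, 10% loss. Visits are day 1 and weeks 1, 2, 4, 8 and 12.

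**Inputs assumed, because the documents do not give them.** Within-patient correlation r (compound symmetry), SDs at visits other than week 4, and the coding of time. For the error rates the true difference is set to the margin (at every visit in the linear case), with 102 per arm and complete data. Center and baseline are left out of the formulas.

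**Step 1: the plan's own figure.** n = 2 × (1.960 + 1.2816)² × 2.2² / 1² = 101.7, so 102 per group. Then 102 / 0.90 = 113.3, so 114. Both stated figures reproduce.

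**Step 2: categorical visit, equal SDs.** The week-4 contrast is the difference of the week-4 means. True SE = √(2 × 4.84 / 102) = 0.308. The independence model uses the residual variance pooled over six visits, which is also 4.84, so its SE is 0.308. False non-inferiority = Φ(−1.96 × 0.308/0.308) = 2.5%, whatever r is.

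**Step 3: categorical visit, unequal SDs.** The true SE stays 0.308, but the model SE uses the pooled variance (5 × s² + 4.84)/6, where s is the SD at the other five visits.

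| s | pooled variance | model SE | ratio to 0.308 | false non-inferiority |
|---|---|---|---|---|
| 1.8 | 3.507 | 0.262 | 0.851 | 4.8% |
| 2.0 | 4.140 | 0.285 | 0.925 | 3.5% |
| 2.6 | 6.440 | 0.355 | 1.154 | 1.2% |

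The last column is Φ(−1.96 × ratio).

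**Step 4: linear time.** The week-4 difference is now read off two fitted lines. Visit j has weight 1/6 + (4 − 4.524)(t_j − 4.524)/106.23, with t in weeks. The weights sum to 1 and their squares sum to 0.1692.

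- Model SE = √(0.0949 × 0.1692) = 0.127, where 0.0949 = 2 × 4.84/102.
- True SE = √(0.0949 × [(1 − r) × 0.1692 + r]).

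| r | true SE | ratio | false non-inferiority |
|---|---|---|---|
| 0.4 | 0.218 | 0.581 | 12.7% |
| 0.5 | 0.236 | 0.538 | 14.6% |
| 0.6 | 0.252 | 0.503 | 16.2% |

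**Step 5: does a patient random intercept repair it?** This was simulated with 4,000 trials per case, 102 per arm, r = 0.5 and baseline adjustment (baseline correlation 0.3).

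| case | error rate without patient term | error rate with patient term |
|---|---|---|
| linear time | 14.7% (model SE 0.121, empirical 0.219) | 2.4% (model SE 0.215) |
| categorical, equal SDs | 2.7% (model SE 0.293) | 2.7% (model SE 0.294) |
| categorical, other SDs 1.8 | 4.75% | 4.75% |

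The intercept cures the linear case, changes almost nothing in the equal-SD case, and leaves the unequal-SD case as it was. There the cause is one residual variance shared by all visits.

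**The case against.** The strongest reply is that the section is silent rather than wrong. Naming center as a random effect does not exclude correlated residuals. A model with an unstructured residual covariance needs no patient random effect, and the covariance and time coding may sit in an analysis plan that is not shown. The secondary and subgroup sections show that the authors mean to allow for repeated measures. This has some force: the intent is visible. But the article does state a random-effects structure for the primary model, and it differs from the one stated for the same score elsewhere. That is an inconsistency in the text, in the model where it matters most.

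The reply is also right on several stronger points that a reader might infer:

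- **That the interval is bound to be too narrow.** With categorical visits and equal SDs it is unaffected, and with larger SDs at other visits it is conservative.
- **That the trial faces a 13% to 16% error rate.** This needs linear time, which the protocol nowhere states. A week-4 target and irregular visits point rather to visit-specific contrasts.
- **That two week-4 intervals compete for the decision.** The secondary section speaks of every follow-up time point, but only the primary model's interval is set against the margin, and the list of secondary outcomes omits week 4.
- **That a missing week-4 score gains nothing from the patient's other visits.** The model without a patient term would not borrow from them, but the missing-data section plans multiple imputation under missing at random. The effect of missing data was not calculated here.

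**Conclusion.** The point holds in conditional form. As written, the confirmatory model leaves within-patient correlation and the coding of time unstated, and is out of step with the other leg-pain models. Its week-4 interval is sound only with categorical visit and a common SD (strictly, a pooled variance equal to the week-4 variance).

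Against a nominal 2.5%, the error rate is 2.5% in that case, about 1.2% to 4.8% over the assumed SD range, and about 13% to 16% under linear time with correlation 0.4 to 0.6. The correlations and the SDs at other visits are assumptions, and the direction of the unequal-SD effect is unknown. Equal SDs should not be taken for granted: day-1 scores follow an injectate containing lidocaine, and scores after week 4 may follow a repeat injection.

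The correction is worth making before unblinding, because a model chosen afterwards could look data-driven.

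**What to change.** In Primary outcome analysis, state that visit is a categorical factor and that within-patient covariance is modelled with visit-specific variances (unstructured). Keep treatment, treatment-by-visit, baseline NRS and center, and name the week-4 contrast as the primary estimate. An acceptable alternative is an ANCOVA of the week-4 score alone with baseline NRS and center.

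In Secondary outcome analysis, use the same repeated-measures model for leg NRS at the other visits. Copying the patient random intercept into the primary section would remove the inconsistency, but would not protect the interval if variances differ by visit. Baseline-by-visit terms and Kenward-Roger degrees of freedom are reasonable choices, not needed to correct the error.

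The cost is a change of wording and slightly more analysis work. The sample size stays at 102 per group, 114 after loss, and no data collection changes.
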